### Assessment at 24 months

A final evaluation of the cognitive function of all trial participants will be carried out after 24 months of intervention. Participants will be invited to attend their general practice and will be assessed for:

1. Psychological health: as at baseline.

2. Blood pressure: as at baseline.

3. Cardiovascular health: record of hospital admissions for MI or stroke between the 21 and 24 month appointments.

4. Basic anthropometric measures: as at baseline.

5. Buccal cell DHA concentration: as at baseline. Collected as a marker of the impact of the intervention on buccal cell DHA concentration, and compliance in the intervention arm of the trial.

6. Cognitive function: as at baseline.

Participants will be offered the use of a taxi, or their travel costs on public transport or mileage in private cars to attend the appointment up to a maximum of £10.

### Data analysis for assessing change in cognitive function

Primary analysis will be carried out based upon the groups as randomised ("intention to treat"). Results will be presented as appropriate effects sizes with a measure of precision (95% confidence intervals). Covariates such age, gender, and baseline blood pressure and DHA concentration will be adjusted for in the analysis. Further exploratory analyses will be based on those patients who fully follow the treatment protocol.

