#### (ii) Patients

Participating general practices, will draw a sample of healthy, cognitively-normal adults aged 70–79 years from their practice registers. These potential participants will be pre-screened for eligibility, by study nurses employed by each practice, using available clinic records and a GPRF computer identifier programme. Individuals currently diagnosed with either diabetes (Type I or Type II) or dementia will be excluded. The exclusion of individuals with diabetes is necessary as these individual will have raised susceptibility to vascular and neural damage and may therefore be less sensitive to the proposed intervention. Individuals with pre-diagnosed dementia will be excluded as the intervention is aimed at delaying cognitive decline in people who are currently not demented. The list of potential participants will be checked by the named General Practitioner in the clinic who will use discretion to exclude individuals not deemed suitable to take part in the study (e.g. recent bereavement, terminal illness).

Eligible individuals identified by this process will each receive a letter and information sheet from their general practice outlining the nature and importance of the study. The letter will also act as a screen for potential participants who are currently consuming fish-oil supplements. Participants reporting the current daily use of fish-oil supplements will be excluded from the trial. Potential participants will be invited to make an appointment with the research nurse at their local general practice. Participants will be offered the use of a taxi, or their travel costs on public transport or mileage in private cars to attend the appointment up to a maximum of £10. The invitation letter will explicitly state that if they do not wish to take part in the study, it will not prejudice the quality of health care provision from their general practice.

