Individuals giving informed consent will be enrolled in the trial. The research nurse will telephone the central randomisation service to register the participant, giving identifying details and the participant's age. Randomisation will allow secure blind allocation of eligible people to one or other arm of the study. Following random allocation a study number will be given for each study participant. This will also be used to identify the supply of capsules to be prescribed for each participant. The study number will be entered on the participant's entry form. Pre-labelled identical-looking packs of capsules (see *Dietary Intervention *below) will be stored securely in the general practice. Minimisation criteria will be used to ensure a balance of key prognostic factors using the following two criteria: age group (70–74 and 75–79 years) and general practice.

Participants will then be assessed by completing questionnaires and undertaking a series of tests (see *Baseline Data Collection *below). The full set of baseline tests will take approximately 60 minutes to complete. Any couples recruited to the study will undertake their assessments separately. Participants will be provided with the contact details of the study nurses and trial manager. Information will also be available from the trial web-site [17] for those participants who wish to use this method of obtaining information. Participants will be thanked for their time and co-operation.

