### Sample size

The sample size required for this trial is based on a 0.3SD difference between trial arms in long-delay free recall of List A of the California Verbal Learning Test over the 24 months of intervention. To detect a 0.3SD difference between trial arms, with 90% power and 1% significance, 332 individuals are required per treatment group. Allowing for 20% drop-out over 24 months of intervention, the total sample size required for the study is 798 individuals. A difference of 0.3SD is clinically relevant and would be equivalent to individuals in the intervention arm being able to remember one more word out of the 16 in the California Verbal Learning Test than those in the placebo arm [18].

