### Baseline data collection

1. Psychological health: the 30–item General Health Questionnaire (GHQ-30) will be used to assess the affective state of participants [19]. The GHQ-30 is quick and easy to administer, and an assessment of mood is important as it may be associated with cognitive performance.

2. Educational achievement: the widely used Burnham Scale of educational achievement will be used [20]. This is an important covariate as educational level has been shown to be strongly related to cognitive performance.

3. Blood pressure: this is necessary as hypertension is an important consequence of the metabolic syndrome, and individuals with high blood pressure may have a raised susceptibility to vascular and neural damage. Baseline blood pressure will therefore be used as a covariate in analysis. Blood pressure will be measured using the automated DYNAMAP device. Two measurements each of systolic and diastolic pressure will be taken in the sitting position (the mean of the two measurements will be used in analysis); participants will have rested for 5 minutes before their blood pressure is measured and there will be a minimum of 5 minutes between the two measurements. Normal general practice procedures will be followed for the management and treatment of high blood pressure.

4. Cardiovascular health: any history of hospital admission for myocardial infarction (MI) or stroke over the preceding 5 years will be abstracted from patient notes.

5. National Health Service number: So that the study organisers do not lose contact with patients should they move address and also to follow up on health status, participants are being asked to give their agreement for their names and NHS numbers to be sent to the NHS Central Register.

6. Basic anthropometric measures: height and weight will be measured using standardised procedures in order to enable the calculation of the Body Mass Index: a basic marker of body size.

7. Swab of cheek cells: nurses will collect a sample of buccal mucosal epithelial cells from each participant. This is a relatively non-invasive procedure in which a sterile wooden spatula is scraped briskly along the inside of the cheek (about 10 strokes on each cheek). The cheek cells will be sent to laboratories, in sterile containers, to be analysed for their n-3 LCP concentration.

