### Recruitment

Following the initial selection of 20 general practices to be involved in the trial, 4–6 of these practices will be selected to take part in the retinal function study. Potential participants from these general practices will be informed about the retinal function study as well as the cognitive function study, and will be invited to take part in both studies.

During the initial meeting at the general practices, the research nurses will fully outline the nature of the trial to potential participants, and in addition, the nurses will describe the objectives and methods of the retinal function tests. Potential participants who remain interested in taking part in either the cognitive study or the cognitive and retinal function study, will then be asked to give consent to undergo a short cognitive screen, the MMSE (as outlined above). Participants who have an MMSE score of greater than or equal to 24 will be invited to give full, informed consent to take part in the cognitive function study. Individuals unwilling to participate further will be thanked for their time and co-operation.

Sufficient information about participants giving informed consent to take part in the cognitive function study will be transmitted to the central randomisation service to allow random allocation to one or other arm of the study. The allocation will be minimised by age group (70–74 and 75–79 years) and centre. Participants will then undergo the series of tests outlined above for the cognitive function study (see *Baseline cognitive function data collection*).

After the collection of baseline cognitive function data participants will be invited to consider the retinal function study. Participants will be free to opt in or out of the retinal function study. It will be explicitly stated that refusing to take part in the retinal function study will not prejudice the quality of treatment and support that they will receive in the cognitive function study or from the general practice. Participants expressing an interest in taking part in the retinal function study will be asked for consent to carry-out a simple visual test (the Logmar test) and respond to a few questions on eye health.

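### Cognitive study: naming general practice (a minimisation factor) and education in the primary model would be a small, nearly free gain in precision

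*Protocol article*

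**What the plan says.** All places are in the protocol article.

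- **Allocation.** The section on patients describes minimisation "using the following two criteria: age group (70–74 and 75–79 years) and general practice" and presents both as prognostic factors to be balanced. The recruitment section of the retinal study says the same with a different word for practice: "The allocation will be minimised by age group (70–74 and 75–79 years) and centre".
- **Analysis.** The data analysis section of the cognitive study says: "Covariates such age, gender, and baseline blood pressure and DHA concentration will be adjusted for in the analysis". No section mentions a practice effect in the analysis.
- **Education.** Under baseline data collection, the item on educational achievement gives this reason for collecting it: "This is an important covariate as educational level has been shown to be strongly related to cognitive performance". The analysis section does not name it. Blood pressure, which the same baseline list marks for adjustment, is named.
- **Setting.** There are 20 practices. On the nurses, the section on patients says: "These potential participants will be pre-screened for eligibility, by study nurses employed by each practice". The 24-month cognitive assessment takes place at the participant's own practice.
- **Outcome.** The primary outcome is change in cognitive function at 24 months on the California Verbal Learning Test.

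**The concern.** When allocation is balanced within practice, differences between practices largely drop out of the true sampling error of the arm comparison. A model without practice does not know this. It counts the between-practice variance as residual error and reports a standard error that is too large for the design. The interval is then wider than it need be, the test is conservative, and some of the precision gained by minimising on practice is not used.

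Of the two minimisation factors, age is named for adjustment and practice is not. Education is a separate matter, because it played no part in allocation. There the baseline section and the analysis section simply do not match.

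**Working it through.** **Inputs from the sample size section.** "To detect a 0.3SD difference between trial arms"; "with 90% power and 1% significance, 332 individuals are required per treatment group". Sidedness is not stated.

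**The plan's own figure.** For two means with SD 1, n per arm = 2(z₁₋α/₂ + z₁₋β)²/d² = 2(2.576 + 1.282)²/0.3², which gives 331 when rounded up. The plan states 332, so the figure is reproduced with a two-sided 1% level. A one-sided level gives 290 and does not reproduce it. Power at 332 per arm is 90.1%.

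**Assumed input.** The ICC is the share of outcome variance that lies between practices. The documents give none, so 0.02, 0.05 and 0.10 are assumed. Because the outcome is a change, this is the ICC of change, not of score level.

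**Set-up.** Total SD is 1, there are 332 per arm, and the arms are balanced within practice.

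- Standard error reported without practice: √(2/n) = √(2/332) = 0.0776.
- True standard error, and the one reported with practice in the model: √((1 − ICC)·2/n).
- Ratio of the two: 1/√(1 − ICC).
- Actual level of the nominal 1% test without practice: 2[1 − Φ(2.576/√(1 − ICC))].
- Power without practice: Φ((0.3 − 2.576 × 0.0776)/true SE).
- Power with practice: Φ(0.3/true SE − 2.576).

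**Example at ICC 0.05.** The true SE is 0.0776 × √0.95 = 0.0757, and the ratio is 1/√0.95 = 1.026. The actual level is 2[1 − Φ(2.643)] = 0.0082. Power is 90.7% without practice and 91.8% with it.

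| Assumed ICC | SE and CI too wide by | Actual level of 1% test | Power, practice omitted | Power, practice included | Points lost |
|---|---|---|---|---|---|
| 0.02 | 1.0% | 0.93% | 90.4% | 90.8% | 0.4 |
| 0.05 | 2.6% | 0.82% | 90.7% | 91.8% | 1.1 |
| 0.10 | 5.4% | 0.66% | 91.3% | 93.3% | 2.0 |

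Power without practice is above 90.1% in every row. With total SD held at 1, balance within practice reduces the true sampling error even when the model ignores it.

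**Simulation check.** With 20 practices of 32 participants, exact balance within practice and 10,000 runs under no effect, the ratio of standard errors was 1.010, 1.025 and 1.052. The 1% test without practice rejected in 0.89%, 0.90% and 0.68% of runs. With practice as a fixed effect it rejected in 0.95%, 1.09% and 0.99%. The Monte Carlo standard error near 1% is √(0.01 × 0.99/10,000), about 0.1 points, so these agree with the table.

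**Degrees of freedom.** The plan says: "Allowing for 20% drop-out over 24 months of intervention, the total sample size required for the study is 798 individuals". That leaves 798 × 0.8 = 638 completers, and a fixed effect for 20 practices uses 19 degrees of freedom. At about 319 per arm the power lost is similar: 0.5, 1.2 and 2.2 points at the three ICCs.

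**Education.** The documents give no correlation between education and 24-month change, so its gain is not quantified.

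**The case against.** The strongest reply is that nothing here is wrong. The covariate list is introduced as a set of examples, the article condenses a fuller protocol, and an analysis plan that is not shown may already contain practice and education. This largely stands. A reader might infer that practice is excluded from the model, or that education has been dropped, but the text supports neither. What remains is that the article does choose which covariates to name, and its choice does not match its own allocation and baseline sections.

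Second, the outcome is a change and participants are reassessed at their own practice. Stable differences in nurse style, site or case-mix therefore cancel. This also stands, and it points to the low end of the ICC range. What does not cancel is a change of nurse, drift in how the test is given, or practices that differ in rate of decline. The General Practice Research Framework trains and monitors the nurses centrally, which should reduce the first two.

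Third, a reader might infer that nurse differences are the dominant source of measurement error. The documents do not show this. The sentence about nurses employed by each practice concerns pre-screening, and nothing says that there is one nurse per practice.

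Fourth, a reader might extend the point to the retinal analysis, whose covariate list is similar. The documents do not support that. All retinal testing is at one hospital, so the tester is not tied to practice. Participants opt in after randomisation, so balance within practice is not assured in that subset. With 22 required per group, extra model terms also cost relatively more.

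**Conclusion.** The point holds as a low-severity improvement to the cognitive analysis only. If the primary model contains just the covariates named, its interval will be slightly too wide and its test slightly conservative, by the amounts in the table. The error is in the safe direction: the effect estimate is not biased and the type I error is not inflated. Even with practice omitted, power at 332 per arm stays above the planned 90% across the assumed range.

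This rests on three assumptions: an ICC for change of 0.02 to 0.10, which the documents do not supply; near-balance of arms within practice, which minimisation is meant to produce but does not guarantee exactly; and a primary model that goes no further than the named list. At an ICC near zero the gain vanishes, and little is lost by adjusting.

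**What to change.** In the data analysis section of the cognitive study, name as prespecified covariates in the primary model:

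- general practice, as a random intercept or a fixed effect;
- age or age group, so that both minimisation factors are in the model;
- educational achievement, in line with the baseline section.

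If the analysis plan already contains these terms, a short cross-reference is enough. The cost is one sentence and about 19 of more than 600 degrees of freedom for practice as a fixed effect. No new data are needed, because the practice number is recorded at trial entry and education at baseline. The retinal analysis needs no change on this account.

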## Cognitive function study

### Outcome measures for cognitive function study

#### Primary outcome

Change in cognitive function at 24 months determined by the California Verbal Learning Test. This is a test of memory of 16 words.

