#### Secondary outcomes

Cognitive performance as measured by immediate and delayed recall of a short story, tests of prospective memory, timed letter search/cancellation task, verbal fluency, digit span forwards and backwards, symbol digit modalities test, simple and choice reaction time, and spatial memory.

Psychological health.

Compliance determined by counting the number of capsules remaining every 3 months, and by measuring the change in n-3 LCP concentration in buccal epithelial cells over 24 months.

Blood pressure.

Change in Body Mass Index (a measure of body size).

Number of hospital admissions for cardiovascular events over 24 months.

Death.

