8. Fish consumption: two simple questions regarding habitual fish consumption will be asked. Firstly, a question regarding the frequency of fish consumption, and second, participants will be asked to list the three species of fish they consume most frequently.

9. Cognitive ability: the participants will be asked to complete a validated series of cognitive tests. It is currently not known which, if any, cognitive domain will be most affected by n-3 LCP supplementation and therefore a series of tests have been selected which cover the major domains (memory, attention, psychomotor speed and executive function):

a. Brief assessment of subjective symptoms of cognitive impairment (memory, language/word-finding, concentration).

b. Immediate and delayed recall of a short story (from the Wechsler Memory Scale).

c. Immediate and delayed recall of a 16-item word list (California Verbal Learning Test).

d. Three tests of prospective memory i.e. remembering to carry out instructions without being reminded.

e. Timed letter search/cancellation task (attention/psychomotor speed/executive function).

f. Verbal fluency – naming animals (word-finding/executive function).

g. Digit span forwards and backwards (working memory/executive function) from the Wechsler Adult Intelligence Scale.

h. Symbol digit modalities test (attention/psychomotor speed/executive function).

i. Simple (psychomotor speed) and choice (decision speed) reaction time.

j. Spatial memory (memory/visual spatial function).

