### Data collection at 3, 6, 9, 12, 15, 18, and 21 months

Participants will have appointments to meet the research nurse every 3 months throughout the study (8 repeat visits in total including 24 month assessment). During these appointments, participants will be reminded of the importance of the study and of the need to comply with the study protocol. The research nurses will also record any information the participants volunteer regarding any discomfort caused by the capsules. The recognised side-effects of n-3 LCP capsules include belching, flatulence, abdominal discomfort and loose stools. These discomforts are generally mild and decrease over time, and the research nurses will provide reassurance to any concerned participants.

Participants will be asked to bring their dietary capsule containers with them to the meeting so that any remaining capsules can be counted as a measure of compliance. Buccal cell swabs will also be taken during these repeat appointments from a random 20% sample every 6 months (i.e. at 6, 12 and 18 months) as a further measure of compliance. Participant records from the general practice will be consulted every 3 months in order to record any hospital admissions for MI or stroke over the intervening 3 month period.

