### Data analysis for assessing change in retinal function

Primary analysis will be carried out based upon the groups as randomised ("intention to treat"). We will test between group differences in change in rod sensitivity over the 24-month follow-up. We will carry out secondary outcome analysis on change in colour vision based on colour contrast specificity. Covariates such as age, gender, and baseline blood pressure and DHA concentration will be adjusted for in the analysis. Results will be presented as appropriate effects sizes with a measure of precision (95% confidence intervals). Further exploratory analyses will be based on patients fully following the treatment protocol.

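### The exploratory adherence analysis compares full adherers only, a post-randomisation subset; a complier-average estimate from the planned capsule counts would be a sounder main adherence analysis

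*Protocol article*

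**What the plan says.** The protocol article makes intention to treat the primary analysis in both studies. In the section on data analysis for the cognitive function study it then adds: "Further exploratory analyses will be based on those patients who fully follow the treatment protocol". The retinal function study has almost the same sentence: "Further exploratory analyses will be based on patients fully following the treatment protocol". The article gives no threshold for full adherence and names no other adherence estimator.

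The primary outcome of the cognitive study is a memory test: "Change in cognitive function at 24 months determined by the California Verbal Learning Test. This is a test of memory of 16 words". The baseline battery, repeated at 24 months, also includes "Three tests of prospective memory i.e. remembering to carry out instructions without being reminded".

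Adherence is to be measured in all participants. The secondary outcomes list "Compliance determined by counting the number of capsules remaining every 3 months", together with n-3 LCP concentration in cheek cells. The section on the 3-monthly visits states the aim, that "any remaining capsules can be counted as a measure of compliance". The count relies on what participants carry back to the clinic: "Participants will be asked to bring their dietary capsule containers with them to the meeting". The same section lists gastrointestinal side effects of n-3 LCP capsules and describes them as usually mild and lessening with time.

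**The concern.** Restricting the analysis to full adherers selects participants on something that happens after randomisation. In most trials the link between adherence and outcome is a general worry. Here it is more specific, because a daily capsule routine over 24 months has to be remembered and the primary outcome measures memory.

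A link with memory is not enough to bias the comparison between arms. The selection must also differ between arms. The document offers two possible routes: gastrointestinal effects felt after swallowing, which identical-looking capsules do not remove, and, if the trial hypothesis is true, a treatment effect on memory that changes who keeps adhering.

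At stake is how a null or weak intention-to-treat result is read. The effect in those who took the supplement is then the natural next question, and the full-adherer comparison is the only answer that the article names.

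**Working it through.** **1. Design figures.** The sample size section gives 0.3 SD, 90% power, 1% significance, 332 per group, 20% drop-out and 798 in total. With a two-sided test (sidedness is not stated), n = 2(2.576 + 1.282)² / 0.3² = 330.7, so 331 per group, which reproduces the 332. After 20% loss, 399 × 0.8 ≈ 319 per arm remain, and the standard error of the intention-to-treat difference is √(2/319) = 0.079 SD. The document gives no figure for the adherence analysis, so every adherence input below is an assumption.

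**2. Bias of the full-adherer comparison, adjusted for baseline score.** Assumed: about two thirds adhere, the log-odds of adherence rise by 0.5 to 1.0 per SD of memory, and they are lower by 0.5 to 1.0 in the active arm. From log-odds ln 2 = 0.693, these shifts give about 55% and 42%, a gap of 12 to 24 points. Averaging over memory brings the smallest gap down to about 10 points.

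| Scenario | Full adherers only | Complier-average |
|---|---|---|
| No effect, same selection in both arms | 0.00 | 0.00 |
| No effect, lower adherence on active | +0.02 to +0.06 | 0.00 |
| True effect in compliers 0.30, lower adherence on active | 0.32 to 0.36 | 0.30 |

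The top of the range is 0.06/0.3 = one fifth of the design difference.

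**3. A stronger assumed link.** Here adherence depends directly on memory change, placebo adherence is about 69%, and there is no baseline adjustment.

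- No effect, same selection: 0.00 for full adherers only.
- No effect, active adherence 59% or 48%: +0.05 or +0.10 SD; complier-average 0.00.
- No effect, memory–adherence link stronger on active: +0.12 SD; complier-average 0.00.
- True 0.30, with active adherence raised to 73%: 0.28 for full adherers only, 0.30 for the complier-average. The bias can therefore go either way.

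**4. Which exposure to use.** Placebo participants receive no n-3 LCP in their study capsules. Without covariates, two-stage least squares therefore reduces to the intention-to-treat difference divided by mean exposure in the active arm. Take an effect proportional to dose, 0.30 SD for full dose. The simulated intention-to-treat difference is 0.246.

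- Proportion of capsules taken: the mean is about 0.826, and 0.246/0.826 = 0.30.
- Binary indicator cut at 80%: 0.246/0.684 = 0.36.
- Cut at 90%: 0.246/0.439 = 0.56.
- Cut at 95%: 0.246/0.23 = 1.07.

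A binary indicator for full adherence fails because partial takers also benefit. The proportion recovers the true value.

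**5. Precision.** For all-or-none adherence p on the active arm, the standard error is 0.079/p: 0.158, 0.113 and 0.088 SD at p = 0.5, 0.7 and 0.9. The test statistic is essentially unchanged. At p = 0.7, 0.21/0.0792 = 2.65 by intention to treat and 0.30/0.113 = 2.65 for the complier-average estimate. It therefore adds no power.

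**The case against.** Much of the case on the other side stands.

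- **Status.** The analysis is labelled exploratory beside a primary intention-to-treat analysis. The article is condensed, and an unseen analysis plan may define full adherence or add another estimator. The lack of a threshold is therefore not itself a fault, and the point concerns only the method that the article does name.
- **Memory link.** A reader might infer that the subset selects on memory as a matter of fact. No section says so. The MMSE cut-off, the advice to tie capsules to a daily routine, reminders to collect supplies and 3-monthly nurse contact all weaken the link.
- **Unconditional bias.** A reader might infer that the comparison is biased whatever happens. It is not: symmetric selection gives 0.00 under the null. Identical capsules make similar selection likely, and the side effects are described as mild.
- **Size.** No section supports the assumed gaps. A bias of 0.02 to 0.06 SD is below one standard error (0.079) of the intention-to-treat difference.
- **Perfect daily adherence.** Read literally, full adherence over some 730 days would leave very few people. Adherence is measured by 3-monthly counts, so the document does not support that reading.
- **Retinal study.** Its primary outcome is rod sensitivity by electroretinogram, so the memory argument does not carry over.
- **Remedy.** The estimate largely rescales intention to treat, and containers may be forgotten by those with poorer memory.

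The remaining objection, that a binary complier-average estimate can mislead, is met by using the proportion of capsules taken.

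**Conclusion.** The concern holds in a limited form. The named adherence analysis is a post-randomisation subset, in a trial where adherence plausibly depends on the domain being measured. It is biased if that selection differs by arm: about 0.02 to 0.06 SD under the main assumptions, against a 0.3 SD target, and up to about 0.12 SD under stronger ones. It is not biased under the null if selection is the same in both arms. The direction and size in this trial cannot be known from the document.

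A sounder method is available from data already planned. The importance is low, since no primary conclusion depends on this analysis.

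**What to change.** In the data analysis section of the cognitive function study:

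1. Keep intention to treat as primary.
2. Make the main exploratory adherence analysis a complier-average estimate by two-stage least squares. Randomised arm is the instrument, the proportion of n-3 LCP capsules taken (from the 3-monthly counts) is the exposure, and the covariates are those of the primary model. Do not use a binary full-adherer indicator.
3. Keep any full-adherer comparison only as a descriptive table, labelled non-randomised, with a capsule-count threshold fixed before unblinding.
4. State the limits. The estimate assumes that allocation acts only through capsules taken and, when read as a full-dose effect, that benefit is proportional to the share taken. Its interval is wider than the intention-to-treat one and it adds no power. It relies on returned containers and does not repair missing 24-month outcomes, with 20% drop-out expected.

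The same change can be made for the retinal function study, but only on the general grounds of post-randomisation selection and tolerability.

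The cost is a change of wording and one extra model on data already to be collected.
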